**Figure 3 figure3:**
[figure not shown]
Resting-state brain connectivity matrix before acupuncture stimulation (A) and after acupuncture stimulation (B).

### Data Collection, Monitoring, and Dropout Criteria

#### Data Collection and Adverse Events Monitoring

Demographic information (age, sex, height, and weight), medical history, and concomitant medication will be collected for each participant at the start of the study. Researchers will record blood pressure, body temperature, respiratory rate, and pulse rate in visits 0 and 1. All adverse events will be fully reported in case report forms, and the association between the adverse events and intervention will be evaluated as not related, possibly related, or related. Severity will be evaluated as mild, moderate, or severe. When severe adverse events, including death, life-threatening events, and the need for hospital admission, occur, the investigator will suspend all or part of the clinical trial and notify other investigators and the Institutional Review Board within 24 hours.

#### Dropout Criteria

The participants will be excluded in the following cases: severe adverse events occur; difficulty proceeding with the trial due to adverse events; the participant or a legal representative wants to stop the trial; the participant withdraws consent to join the trial; the participant fails to finish the interview or the fNIRS scan; and progression of the trial is considered inappropriate by the principal investigator.

### Statistical Analysis

Only data from participants who completed the fNIRS scan, cognitive function test, and measurement of CR will be contained in the statistical analysis. All categorical data are presented as frequencies or percentiles and will be analyzed using the chi-square or Fisher’s exact test. All numerical data will be presented as the mean and standard deviation and analyzed using an independent *t* test or Wilcoxon rank-sum test. Preprocessing and analyses of fNIRS data will be performed using MATLAB and the NIRSIT analysis tool.

A two-sample *t* test will be performed to compare the brain activations and connectivity between the groups with and without cognitive impairment. A paired *t* test will be conducted to compare the brain activations and connectivity before and after acupuncture stimulation. The CR values from CRIq will be applied for correlation analysis in the form of continuous variables or divided into binary groups (high and low CR) by mean values for subgroup analysis. Since the expression of CR may appear differently depending on the disease status, a subgroup analysis will be conducted by dividing the healthy control and the patient group. Mixed model analysis will be adjusted to determine the interaction effect of intervention and CR in both groups. Pearson correlation will determine the CR-related brain connectivity or clinical score–related metrics. If there is a significant age difference between 2 groups, the age factor will be added as a covariate in the analysis to adjust the effect of age as much as possible.

Statistical significance in fNIRS imaging would be explored using uncorrected and corrected levels (false discovery rate and family-wise error). At the uncorrected level, uncorrected *P*<.001 will be used, and at the corrected level, *P*<.05 will be applied.

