## Methods

### Trial Design, Setting, and Aim

This study will be a single-center, block-randomized, placebo-controlled, parallel-group clinical trial. The study will be conducted at the College of Korean Medicine at Sangji University. This protocol complies with the SPIRIT (Standard Protocol Items: Recommendations for Interventional Trials) guidelines [25]. The aim of this study is to investigate the acute neural mechanisms of acupuncture stimulation concerning CR and to identify the neural substrates of CR in the group without cognitive impairment and the group with cognitive impairment using fNIRS.

The participants will be divided into 2 equal groups: the verum acupuncture group (study group) and the sham acupuncture group (control group). After each group is confirmed to participate in the study through screening (visit 0), fNIRS scanning and acupuncture manipulation will be conducted at visit 1. Cognitive function assessments, including the Korean version of the Mini-Mental State Examination (MMSE-K) and Montreal Cognitive Assessment (K-MoCA), will be conducted during screening. At visit 1, each participant will be measured twice using fNIRS (first and second scan) before and after acupuncture stimulation. Finally, CR marker assessment, such as the Cognitive Reserve Index Questionnaire (CRIq), will be conducted through interviews in visit 1. The period between visit 0 and visit 1 will not exceed 1 week. Participant recruitment was initiated on August 22, 2023, and the study is scheduled to continue until February 2025. The flow chart is illustrated in Figure 1, and the overall procedure is presented in Table 1.

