**Enrollment**					
	Eligibility screen	✓			
	Informed consent	✓			
	Randomization and allocation	✓			

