#### Study Procedures

All participants will be subjected to measurement of vital signs (blood pressure, pulse rate, and temperature), demographic information, and medical history (past, present, and family). Cognitive function assessments (MMSE-K and K-MoCA) will also be performed during visit 0 (screening). Eligible participants who meet the inclusion and exclusion criteria will receive the schedule for visit 1.

At visit 1, the investigator will check the participant’s vital signs and changes in medication, perform 2 fNIRS scans before and after acupuncture stimulation, and assess the level of CR using CRIq. For medications, the investigator will check for changes but will not specifically allow or restrict certain drugs. According to stratified randomization, the participants will be assigned to 2 acupuncture stimulation groups. Acupuncture stimulation will be performed by a Korean medicine doctor with >3 years of clinical experience. fNIRS scans consist largely of 2 main parts: a 5-minute resting state scan and a task scan of working memory.

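### The completers-only rule removes randomised participants from the verum-sham contrast, including some for lacking a CRIq that the contrast does not need

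*Protocol article*

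**What the plan says.** The Statistical Analysis section gives the only analysis-population rule in the protocol article, and it covers the whole analysis: "Only data from participants who completed the fNIRS scan, cognitive function test, and measurement of CR will be contained in the statistical analysis".

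The timing of the three named items differs:

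- **Cognitive tests.** MMSE-K and K-MoCA are done at visit 0 and used for eligibility.
- **fNIRS.** "At visit 1, each participant will be measured twice using fNIRS (first and second scan) before and after acupuncture stimulation" (Trial Design, Setting, and Aim).
- **Cognitive reserve.** The same section says that the CRIq assessment "will be conducted through interviews in visit 1".

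Table 1 ticks "Randomization and allocation" at visit 0, and visit 1 follows within a week.

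Under Dropout Criteria, the grounds include adverse events ("The participants will be excluded in the following cases: severe adverse events occur; difficulty proceeding with the trial due to adverse events"), incomplete assessment ("the participant fails to finish the interview or the fNIRS scan") and judgement ("progression of the trial is considered inappropriate by the principal investigator").

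Outcome Measures lists three primary outcomes. The second, change in activation in verum versus sham, is the only one that compares randomised groups. The other two compare disease-status groups and high versus low CR.

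**The concern.** A rule that selects on what happens after allocation can make the analysed arms differ from the randomised arms. Two of the three completion conditions do this.

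- **Second scan.** It follows needling, and the needling differs sharply between arms. Verum is deep, manipulated repeatedly and meant to produce deqi; sham is 1-2 mm deep and left in place. If some participants cannot finish because of what they received, those remaining in verum are a selected group.
- **CRIq.** It is needed for the CR analyses but not to compare verum with sham. Someone with both scans and an unfinished interview is discarded from primary outcome 2 for no analytic reason. Unfinished interviews are foreseeable: Results reports that 16 of the 20 impaired participants enrolled so far have dementia.

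At stake are some bias in the one randomised primary contrast and an avoidable loss of data where cells hold only about 10-15 people.

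**Working it through.** **1. Which conditions act after allocation**

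| Condition | When | Effect on randomised participants |
|---|---|---|
| MMSE-K, K-MoCA | Visit 0, for eligibility | Removes few or none |
| First scan | Visit 1, before needling | Loss possible, but nobody has yet been needled |
| Second scan | Visit 1, after needling | Loss could depend on arm |
| CRIq | Visit 1 | Loss possible; not needed for verum versus sham |

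**2. The plan's own figures**

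The planned total is 30 + 30 = 60, allocated 1:1, so about 30 verum and 30 sham. Planned dropout is 10%: 0.10 × 60 = 6 participants, leaving 54. Per cell of 15 it is 0.10 × 15 = 1.5, that is 1-2 people.

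The stated 10-15 per group cannot be reproduced, because no effect size or SD is given. Solving backwards at 80% power and two-sided 5% (sidedness is not stated, so this is an assumption), d = (1.960 + 0.842) × √(2/n):

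- n = 10: d = 1.25 (1.33 by the t test)
- n = 15: d = 1.02 (1.06 by the t test)

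These values serve only as a scale for the biases below.

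**3. Illustrative bias**

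Assume no true effect. Let a share f of the verum arm be lost, and let those lost differ by k SD from those retained. With the full-arm mean at 0 and the retained mean m, (1 − f)m + f(m − k) = 0, so m = f × k. That is the bias, taking losses in sham as uninformative. Both f and k are assumptions; the documents supply only the 10% total.

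For the false-positive rate, take one two-sided 5% t test on a per-participant change with SD 1, pooled over disease groups. It has 52 degrees of freedom and noncentrality bias ÷ √(1/n1 + 1/n2).

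| Losses | f | k | Bias = f × k | Analysed | Noncentrality | False-positive rate |
|---|---|---|---|---|---|---|
| Unrelated to arm and outcome | any | 0 | 0 | 54 in total | 0 | 5% |
| 3 per arm, informative in verum only | 3/30 = 0.10 | 0.5 | 0.05 SD | 27 vs 27 | 0.05/0.272 = 0.18 | 5.4% |
| same | 0.10 | 1.0 | 0.10 SD | 27 vs 27 | 0.10/0.272 = 0.37 | 6.5% |
| All 6 in verum | 6/30 = 0.20 | 0.5 | 0.10 SD | 24 vs 30 | 0.10/0.274 = 0.37 | 6.5% |
| same | 0.20 | 1.0 | 0.20 SD | 24 vs 30 | 0.20/0.274 = 0.73 | 11.1% |

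The last two rows are the extreme allocation of losses, not a forecast. The rates refer to a single test and do not carry over to the channel-wise thresholds in the protocol.

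**The case against.** Several stronger readings are tempting, and the protocol does not support them.

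- **That people with adverse events are removed from the analysis and from safety reporting.** A reader might infer this from the word excluded. The list is headed Dropout Criteria and can equally govern leaving the trial. Data Collection and Adverse Events Monitoring has all adverse events recorded in case report forms with causality and severity, and Results commits to CONSORT reporting. What stands is an ambiguity about someone who has complete scans and also meets a dropout criterion.
- **That the protocol contradicts itself on when randomisation happens.** Study Procedures says, in its visit 1 paragraph, "According to stratified randomization, the participants will be assigned to 2 acupuncture stimulation groups", while Table 1 places allocation at visit 0. The two fit if allocation is drawn at visit 0 and applied at visit 1. Under either reading the second scan follows allocation.
- **That losses before the first scan bias the contrast.** Nobody has been needled by then and participants are blinded, so no arm-related mechanism is apparent. These losses mainly cost precision.
- **That a bias of 0.2 SD should be expected.** It needs every loss in one arm and a full 1 SD difference. Treatment is one 15-minute session with both scans at one visit, so losses may be few. Even 0.2 SD is small beside the 1.02-1.33 SD that the sample size implies.

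Two further objections carry weight. First, nothing suggests that CRIq non-completion differs by arm, and the only model in the plan that names the intervention is the intervention-by-CR mixed model, which does need the CRIq. The simple verum-sham contrast still does not, so the data are lost needlessly even if no bias results. Second, a model assuming data missing at random corrects only what observed data predict, and a participant with only a first scan adds little to a change contrast. That limits the fix but does not justify the rule.

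**Conclusion.** The concern holds in a limited form. The protocol fixes a completers-only rule for all analyses, so this is a stated choice and not a detail left to an analysis plan. For primary outcome 2 the rule drops randomised participants who lack a second scan, which could depend on the needling, and those who lack only the CRIq, whom the contrast could keep.

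The size is unknown. About 6 of 60 would be lost at the planned dropout rate. Bias is zero if losses are unrelated to arm and outcome, and about 0.05-0.2 SD if 10-20% of one arm is lost and those people differ by 0.5-1 SD, both assumed. The disease-status and CR contrasts are not randomised and are not affected in this way. The rule should be changed; it does not by itself invalidate the trial.

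**What to change.** - Analyse verum versus sham in the allocated arms, using all available scans from every randomised participant with usable fNIRS data. A mixed model of the kind already named for the CR interaction, here without the CR terms, would serve.
- Require the CRIq only for the CR analyses, and cognitive scores only for analyses that use them.
- Keep the completers analysis as a sensitivity analysis.
- Report losses and their reasons by arm, including those before the first scan, which no scan-based model can recover.
- State that Dropout Criteria governs leaving the trial, and does not remove data already collected from the analysis or from safety summaries. The criteria themselves need not change for this.

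The cost is a change of analysis wording and a little more analysis work, with no extra visits, staff or participants. The price is a missing-at-random assumption that only partly corrects informative loss of second scans. The time of allocation should be left alone: 50 of the planned 60 are already enrolled, and moving it now would split the trial into two procedures without helping those enrolled.

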#### Sample Size

In this study, the number of participants has been determined statistically. In our hypothesis, the significance level (α) and power (1–β) will be set to 5% and 80%, respectively. Then, an effect size will be calculated using an estimated value of the variability in the MMSE-K and K-MoCA scores based on the literature [26]. As a result, the number of samples came out to be about 10-15 for each group (study or control group) to satisfy the criteria of the normal deviates of significance level and power in the healthy controls and patient groups. The anticipated dropout rate was set to 10%. A similar number of subjects (i.e., 10–15 subjects in each group) can be found in the previous neuroimaging studies [27-29].

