### Interventions

In the study group, verum acupuncture stimulation will be conducted for 15 minutes by stainless steel acupuncture (0.25 mm×40 mm, Dongbang acupuncture) on acupoints, which are known to be associated with cognitive functions in previous studies (Baihui [GV20], Sishencong [EX-HN1], Taixi [KI3], Zusanli [ST36], Hegu [LI4], and Taichong [LR3]), and deqi sensation will be induced [24,34,35]. The needle will be lifted and thrust approximately 30-50 mm and twisted and rotated at approximately a 90°-180° angle 60 times/minute (60 Hz). The manipulation will then be performed at 1-minute intervals to maintain the amount of stimulation and achieve deqi sensation. A questionnaire on deqi sensations will be implemented.

For the control group, superficial needling acupuncture (depth of needling: 1-2 mm per nonacupoint) will be performed for 15 minutes using stainless steel acupuncture (0.25 mm×40 mm, Dongbang acupuncture) on nonacupoints. Nonacupoints, which are not related to cognitive function, would be approximately 1 cm away from the acupoints of the study group. The needles for sham acupuncture will remain in place. In the case of superficial needling, manipulation techniques and induction of deqi sensation will not be achieved.

Superficial needling can be a subtype of minimal acupuncture [36]. We thought that the characteristics of acupoints, depth of acupuncture stimulation, intensity of the stimulation, and deqi sensation would all be determinants of acupuncture stimulation. Therefore, we selected minimal acupuncture that lacks these features as a sham control. This type of sham acupuncture has been applied in various studies, including Bell’s palsy, migraine, and chronic musculoskeletal pain syndrome, for a long time [37-40].

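### The completers-only rule covers the whole statistical analysis, so an adverse event summary made under it would omit participants who stopped because of a needling harm

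*Protocol article*

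**What the plan says.** All references are to the protocol article, Methods.

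- **Statistical Analysis** opens with the rule "Only data from participants who completed the fNIRS scan, cognitive function test, and measurement of CR will be contained in the statistical analysis". The next sentence is also general: "All categorical data are presented as frequencies or percentiles and will be analyzed using the chi-square or Fisher’s exact test".
- **Study Procedures** has the investigator at visit 1 "perform 2 fNIRS scans before and after acupuncture stimulation, and assess the level of CR using CRIq". **Trial Design, Setting, and Aim** puts the reserve questionnaire at the end of its list: "Finally, CR marker assessment, such as the Cognitive Reserve Index Questionnaire (CRIq), will be conducted through interviews in visit 1". The cognitive tests are done earlier, at screening.
- **Dropout Criteria**: "The participants will be excluded in the following cases: severe adverse events occur; difficulty proceeding with the trial due to adverse events". Failure to finish the interview or the scan is a further ground.
- **Data Collection and Adverse Events Monitoring**: "All adverse events will be fully reported in case report forms, and the association between the adverse events and intervention will be evaluated". Severity is graded too, and severe events go to the Institutional Review Board within 24 hours.

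No section exempts adverse events from the completers rule. No adverse event analysis is described, and Outcome Measures lists no safety outcome.

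**The concern.** Restricting the imaging analyses to participants with complete imaging is a separate question and is not raised here. The concern is that the same restriction, as worded, reaches safety data. Completion is determined after treatment, and harm from the treatment is one of the things that prevents it. The rule would thus remove the participants who carry most of the information about needling harm.

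Two consequences follow for any adverse event table built on the rule. The overall rate can be understated. The rate of events that end participation reads 0% by construction, whatever happened. If such stops were more frequent in one arm, the comparison between arms would also shrink, and verum could look safer than it is. That is plausible, because in the verum arm "The needle will be lifted and thrust approximately 30-50 mm" with repeated manipulation, while sham needles go 1-2 mm deep and stay still. The document gives no event rates, however, and does not establish it. The figure has some use, since the Discussion offers the study as groundwork for research on longer-term acupuncture in cognitive impairment.

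**Working it through.** The plan states no adverse event figure, so there is none to reproduce. The check has two parts.

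**1. Does the rule reach participants who stop for harm?**

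- Completion requires the scan, the cognitive tests and the reserve measurement.
- The second scan comes after needling. Even if the questionnaire were given earlier in the visit, completion could not be reached before needling.
- A participant who has a needling reaction and does not have the second scan is therefore not a completer. The Dropout Criteria exclude the same person on the separate ground of the adverse event.
- The monitoring section keeps the event in the case report form. That is a rule for recording, not an analysis population.

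So the event is recorded but falls outside the statistical analysis as defined.

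**2. How much could that change a summary?**

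Inputs from the document:

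- 60 planned participants (Abstract: 30 without and 30 with cognitive impairment), allocated 1:1, so about 30 per arm.
- Anticipated dropout of 10% (Sample Size), which is 0.10 × 60 = 6. No cause is given.

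Assumptions:

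- All 60 are needled, and each person counts at most once.
- b = 6 completers have an event (3 per arm).
- s participants stop because of an adverse event, varied from 0 to 6.

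Pooled rates: all needled = (6 + s)/60; completers only = 6/(60 − s).

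| s | All needled | Completers only |
|---|---|---|
| 0 | 6/60 = 10.0% | 6/60 = 10.0% |
| 1 | 7/60 = 11.7% | 6/59 = 10.2% |
| 3 | 9/60 = 15.0% | 6/57 = 10.5% |
| 6 | 12/60 = 20.0% | 6/54 = 11.1% |

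Events that end participation: 1/60 = 1.7%, 3/60 = 5.0% or 6/60 = 10.0% in truth for s = 1, 3 or 6. Under the rule the figure is 0% each time.

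Verum minus sham, 30 per arm, with sV and sS stops in the two arms: all needled = (sV − sS)/30; completers only = 3/(30 − sV) − 3/(30 − sS).

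| Stops, verum v sham | All needled | Completers only |
|---|---|---|
| 3 v 3 | 0 | 0 |
| 1 v 0 | 1/30 = 3.3 points | 3/29 − 3/30 = 0.3 |
| 3 v 0 | 3/30 = 10.0 points | 3/27 − 3/30 = 1.1 |
| 0 v 3 | −3/30 = −10.0 points | 3/30 − 3/27 = −1.1 |

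In these scenarios the completers-only difference is pulled towards zero, and which arm benefits depends on where the stops occur.

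**The case against.** The strongest reply is that no planned analysis is affected. The outcomes are all imaging, network and cognitive measures, and no adverse event test or table is described. The three conditions for completion match the three kinds of data that those analyses use, so the sentence may have been meant only for them. The categorical-data sentence may likewise refer to baseline characteristics such as sex. A safety population is something an article commonly leaves to the full protocol or analysis plan. Adverse events also have their own section, which carries no completers restriction.

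Much of this stands. The narrower reading is possible, the effect is conditional on a summary being made, and no event record is lost. The magnitudes are illustrative. Visits 0 and 1 can be up to a week apart and consent can be withdrawn, so some of the 10% dropout may occur before any needle is inserted. Six stops for harm after a single 15-minute session is an upper bound, not a forecast.

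Two things remain. First, the criticism is not that a safety set is missing. A stated rule is too broad, and a safety set defined elsewhere would have to contradict it. Second, an adverse event summary is foreseeable: the events are a scheduled assessment graded for severity and relatedness, and the Results section promises reporting in line with the CONSORT checklist.

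**Conclusion.** The concern holds, as a minor point. As written, the completers rule would drop participants who stop because of a needling harm from any adverse event summary made under it. The understatement runs from nothing, with no such stops, to 11.1% shown against 20.0% in truth if all six anticipated dropouts were stops for harm. A difference of up to 10.0 points between arms could shrink to 1.1, in either direction. These figures rest on the assumed event counts; only the 60 participants and the 10% dropout come from the document. The imaging, cognitive reserve and cognitive outcomes are not affected by this point.

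**What to change.** In Statistical Analysis, limit the completers sentence to the fNIRS, cognitive reserve and cognitive function analyses. Then add, for example: *Adverse events are summarised descriptively by arm, with severity, relatedness and withdrawals due to adverse events, in all participants in whom any needle was inserted, including those excluded under the dropout criteria.*

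The cost is one or two sentences. The records are already kept under the monitoring section, so no new data, staff or visits are needed. The only downside is that the safety figure may look less favourable.

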**Methods:**

This study is a randomized, placebo-controlled trial. Participants without (n=30) and with cognitive impairment (n=30) will be randomly assigned to the verum or sham acupuncture groups. The verum acupuncture group will receive acupuncture stimulation at acupoints related to cognitive function and gain deqi sensation. The sham acupuncture group will receive superficial needling at nonacupoints not related to cognitive function. Each group will undergo cognitive function tests, functional near-infrared spectroscopy imaging before and after acupuncture stimulation, and an assessment of CR. The primary outcomes will be differences in resting brain activities according to disease status, differences in resting brain connectivity before and after acupuncture stimulation between the 2 groups, and changes in brain activity in relation to the CR index. The secondary outcomes will be brain connectivity or network metrics associated with CR and differences in neural activity between the cognitive task and resting states.

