#### Enrollment, Randomization, and Blinding

Recruitment will be conducted through advertisements on websites and public announcements. Promotion through local communities is also under consideration. The recruitment of participants with cognitive impairment will be promoted through cooperation with community dementia care centers. In this study, in accordance with the recruitment of the participants, the effect of age on brain function will also be investigated; therefore, recruitment in the group without cognitive impairment will not be restricted to older adult participants.

Stratified block randomization will be performed according to sex. Both groups will be assigned in a 1:1 ratio to the study and control groups by applying a block size of 4. Randomization will be conducted using a computer-generated allocation list by an assigned researcher not involved in the assessment or intervention. Participants will be blinded to the type of intervention used. The practitioner will not provide clues regarding allocating information to the participants during the study. Blinding will be maintained until the end of the study. Participants will be asked about their experience of blinding after the end of the study.

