### Outcome Measures

This study aims to explore the immediate neural mechanisms of the acute response to acupuncture stimulation associated with CR in normal aging and disease status and identify the neural substrates of CR.

The primary outcomes will be as follows: (1) differences in brain activation and resting-state brain connectivity according to disease status (the groups with vs without cognitive impairment); (2) differences in brain activation before and after acupuncture between study and control groups (verum acupuncture vs sham acupuncture); and (3) differences in brain activation according to CR (high CR group vs low CR group).

Secondary outcomes are brain connectivity or network metrics (graph theoretic metrics) associated with the CRIq index, differences in brain activity between working memory tasks and resting states, and network metrics associated with cognitive function scores (MMSE-K, K-MoCA).

The brain connectivity matrix will be obtained as Pearson correlation between 48 channels using time-series data during the scan period (Figure 3). Network metrics, including the index of efficiency, clustering coefficient, and centrality, can be calculated using the connectivity matrix by the Brain Connectivity toolbox in MATLAB 2023b (The Mathworks).

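### Primary outcome 2 compares verum with sham in before-after change, but the only test tied to the before/after scans is a paired t test, which does not compare the arms

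*Protocol article*

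**What the plan says.** Outcome Measures lists three primary outcomes. The second is "differences in brain activation before and after acupuncture between study and control groups (verum acupuncture vs sham acupuncture". The abstract words it in terms of connectivity, but it too is between arms: "differences in resting brain connectivity before and after acupuncture stimulation between the 2 groups". It is the only primary outcome that rests on randomisation; the first compares disease status and the third compares cognitive reserve (CR) level.

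Statistical Analysis then names these tests:

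- A two-sample t test, for disease status: this "test will be performed to compare the brain activations and connectivity between the groups with and without cognitive impairment".
- A paired t test, for the two scans: this "test will be conducted to compare the brain activations and connectivity before and after acupuncture stimulation".
- A mixed model: "Mixed model analysis will be adjusted to determine the interaction effect of intervention and CR in both groups".
- Correlation and high/low CR subgroup analyses, for CR and clinical scores.
- A general rule placed before the imaging analyses: "All numerical data will be presented as the mean and standard deviation and analyzed using an independent" t test or a rank-sum test.

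Imaging results are to be explored at uncorrected P<.001 and at corrected P<.05.

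**The concern.** The outcome asks whether change differs between verum and sham. The paired t test asks whether the average change differs from zero. Anything that moves the signal between the two scans in both arms enters the second question and cancels in the first. Examples are elapsed time, signal drift and, for task scans only, practice on the repeated Corsi task. The sham arm is there to remove these shared effects.

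If the text is followed as written, the randomised primary question would be answered either by a pooled before-after test or by two within-arm tests set side by side. Finding significance in one arm and not in the other is not a test of the difference between them.

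**Working it through.** **Matching outcome to test**

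| Analysis named | Target stated in the article | Tests verum vs sham in change? |
|---|---|---|
| Two-sample t test | with vs without cognitive impairment | No |
| Paired t test | before vs after | No, it has no arm term |
| Mixed model | intervention × CR | Not as stated: it asks whether the effect varies with CR |
| Correlation, CR subgroups | CR and clinical scores | No |
| Independent t test or rank-sum | numerical data in general | Could, if applied to change scores; not linked to arms, change or imaging |

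**Inputs for the illustration**

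- Arm sizes: the abstract gives 30 participants without and 30 with impairment, allocated 1:1. That is 30/2 = 15 per arm within a disease group and 60/2 = 30 per arm overall.
- Thresholds: 0.05, from Sample Size ("the significance level (α) and power (1–β) will be set to 5% and 80%, respectively"), and uncorrected P<.001, from Statistical Analysis. Sidedness is not stated; two-sided is assumed.
- Common shift d, in SD of the change score: the article gives no figure. Values of 0.3, 0.5 and 0.75 are assumed, identical in both arms, so the true arm difference is zero.

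**Formulas**

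For a paired t test in n participants, the probability of significance is q = P(|T| > c), where T is noncentral t with n − 1 degrees of freedom and noncentrality d√n, and c is the two-sided critical value. The arms are independent, so the probability of verum significant and sham not is q(1 − q). The pooled paired test uses the same formula with 2n participants.

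Example: n = 15, d = 0.5, alpha 0.05. Noncentrality = 0.5 × √15 = 1.94 and c = 2.145, so q = 0.438. Verum only = 0.438 × 0.562 = 0.246.

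**Results**

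| Threshold | n per arm | d | q, verum significant | Verum only, q(1 − q) | Pooled paired (2n) |
|---|---|---|---|---|---|
| 0.05 | 15 | 0.3 | 19% | 15% | 36% |
| 0.05 | 15 | 0.5 | 44% | 25% | 75% |
| 0.05 | 15 | 0.75 | 77% | 18% | 98% |
| 0.05 | 30 | 0.3 | 36% | 23% | 63% |
| 0.05 | 30 | 0.5 | 75% | 19% | 97% |
| 0.05 | 30 | 0.75 | 98% | 2% | >99% |
| 0.001 | 15 | 0.3 | 1% | 1% | 4% |
| 0.001 | 15 | 0.5 | 4.5% | 4% | 21% |
| 0.001 | 15 | 0.75 | 18% | 15% | 67% |
| 0.001 | 30 | 0.3 | 4% | 4% | 14% |
| 0.001 | 30 | 0.5 | 21% | 17% | 66% |
| 0.001 | 30 | 0.75 | 67% | 22% | 99% |

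A simulation of 100,000 trials at alpha 0.05 agrees with the upper half of the table. In it, a two-sample t test on change scores rejected in 4.9% to 5.2% of trials, whatever the shift. With no shift (d = 0), the paired test rejects at its nominal rate, so the excess comes entirely from the shared shift.

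**Precision of the between-arm alternatives**

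With equal variances at the two scans and correlation ρ between them, the variance of ANCOVA relative to a change-score test is (1 − ρ²) / [2(1 − ρ)] = (1 + ρ)/2. For ρ = 0.3, 0.5 and 0.7 (assumed) this is 0.65, 0.75 and 0.85.

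**The case against.** The strongest defence is that the article does contain the pieces of a between-arm analysis. The mixed model has intervention as a factor, and an interaction of intervention with CR cannot be estimated without the sham arm. Such a model would ordinarily carry an intervention effect and, with two scans per person, might carry arm × time. The general sentence on independent tests, if applied to change scores, would be a valid verum-sham comparison. A condensed article may leave model terms to an analysis plan that is not shown.

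Part of this stands. A reader might infer that the sham arm plays no part in the inference, or that the paired t test is designated as the primary analysis of this outcome. The article supports neither: the mixed model uses the sham arm, though for a different question, and no sentence gives the paired test that status. A reader might also see the absence of sex from the analysis as an error, since "Stratified block randomization will be performed according to sex". A condensed article need not list every covariate, and no conflicting statement is made, so sex belongs only among the refinements.

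The rest does not remove the point. The article is not silent on the before/after data: it names a test for them, and that test does not address the stated outcome. The general sentence is tied neither to the arms nor to imaging. An analysis plan written from this text would carry the mismatch forward.

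The size also needs care. The alpha 0.05 figures describe a single test. At P<.001 the verum-only rate per channel is much lower for small shifts, though not uniformly so: with 30 per arm and a shift of 0.75 SD it is 22%, against 2% at 0.05. Over the device's 48 channels, the chance of at least one such result is higher than the per-channel rate, by an amount that depends on the correlation between channels.

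**Conclusion.** The point holds: primary outcome 2 is between arms, and the only test assigned to the before/after scans is within subjects. No sentence assigns a verum-versus-sham test of change to this outcome.

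This is a mismatch between outcome and test, and it does not depend on the simulated rates. How much it could mislead depends on the shared shift, which is assumed, and on the threshold. Over shifts of 0.3 to 0.75 SD, the verum-only pattern arises with no true arm difference in 2% to 25% of trials at alpha 0.05, and in 1% to 22% per channel at P<.001. Practice on the Corsi task contributes to the shift only if the outcome is read as task activation; for resting scans, time and drift remain.

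**What to change.** State under Statistical Analysis that primary outcome 2 is tested between arms, by one of:

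- ANCOVA of the post-acupuncture value on arm, with the pre-acupuncture value as covariate. Disease group and sex, the randomisation stratifier, can be added as refinements at no cost.
- A mixed model with an arm × time term. Unless the arms are constrained to equal baselines, with two scans this is the change-score test: valid, but less precise than ANCOVA by the ratio (1 + ρ)/2 shown above.

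Report the verum-minus-sham difference with its confidence interval, at the imaging thresholds the article already sets. Keep the paired t tests as descriptive within-arm summaries. The mixed model for intervention × CR can stay for its own question.

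The cost is a change of wording; both scans are already collected for every participant who completes the study.
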